### Participants

Employed persons aged 45 to 59 years will be included. The exclusion criteria are having applied for or used medical rehabilitation services during the last 4 years and previous requests for or receipt of disability pension benefits. Samples will be drawn in equal proportions from the populations of the GPI North (*n* = 22,500) and GPI Central Germany (*n* = 22,500). The samples will be stratified by sex in a ratio of 1:1 and by sickness absence benefits in a ratio of 2:1 (less than 1 week of sickness absence benefits vs. at least 1 week of sickness absence benefits). In the first quarter of the first year, a baseline survey will be performed to assess the 3-month prevalence of back pain (i.e., back pain at any time during the past 3 months including today). The localisation of back pain will be represented on a pain drawing [1]. In accordance with previous large, epidemiological studies in Germany, back pain is defined as pain anywhere in the area between C7 and the gluteal folds [45–47]. Only persons who report some kind of back pain in the baseline survey will be followed in our prospective analysis.

### Sample size estimation

Estimates for baseline response (40%), consent to linking survey with administrative data (80%), back pain (40%) [48], utilisation of rehabilitation (8%) and response to follow-up (60%) are derived from other studies. In case of a 1-to-3-matching of rehabilitants and controls, the final sample of 276 rehabilitants and 828 untreated controls is sufficient to detect a minor difference in the primary outcome between rehabilitants and controls (standardised mean difference = 0.2; two-tailed alpha = 0.05) with a power of 0.82. (Fig. 1).

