#### Propensity score matching

Rehabilitation participants and untreated subjects will be matched by propensity scores to achieve a balanced sample and enable calculation of unbiased estimates of effectiveness [67–72]. The propensity score is the conditional probability of receiving the treatment under evaluation (i.e. the medical rehabilitation programme) given the vector of observed background variables. Matching by propensity scores allows one to obtain a sample in which the treated and untreated groups are balanced, if there is sufficient overlap between their propensity scores. Propensity score matching also allows one to avoid the dimensionality problem that affects conventional direct matching procedures involving multiple variables, e.g. age, sex, socioeconomic state, depression, work ability, by reducing the matching requirement to a single dimension.

The propensity score will be estimated using a logistic regression model including all variables that are associated with treatment allocation. For every treatment case three persons with a similar propensity score will be selected from the larger pool of non-treatment cases. Re-sampling with replacement will be used to reduce bias. If it is necessary to achieve a balanced sample, a caliper of one-quarter of the propensity score will be used during re-sampling. Additional matching schemes will be used in the sensitivity analysis.

Standardised percentage bias will be calculated as an indicator of bias before and after matching due to differences in observed sample characteristics. This is the difference between sample means in the intervention and control groups relative to the square root of the average of the sample variances in both groups [73]. Multiple imputations will be used to fill in missing data before propensity scores are estimated. The propensity scores for each record will be averaged across the completed datasets and propensity score matching will be performed with these averaged scores [74].

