#### Estimating the treatment effect

The average treatment effect for the treated cases will be estimated with weighted linear regression models in the case of continuous outcomes and generalised linear models in the case of binary outcomes (see above: primary outcome and secondary outcomes) [75]. Robust standard errors will be calculated.

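### The stated power of 0.82 treats the 828 controls as different, equally weighted persons, but matching is with replacement; unadjusted power is about 0.79 at best

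*Protocol article*

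**What the plan says.** Three sections of the protocol article bear on this point.

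- **Sample size estimation.** The calculation is framed by the matching ratio ("In case of a 1-to-3-matching of rehabilitants and controls"). It concludes that "the final sample of 276 rehabilitants and 828 untreated controls is sufficient to detect a minor difference in the primary outcome", with the parameters "standardised mean difference = 0.2; two-tailed alpha = 0.05) with a power of 0.82". It mentions neither reuse nor unequal weighting of controls.
- **Propensity score matching.** "For every treatment case three persons with a similar propensity score will be selected from the larger pool of non-treatment cases". The next sentence reads: "Re-sampling with replacement will be used to reduce bias".
- **Estimating the treatment effect.** On the estimator, this part of the plan states: "The average treatment effect for the treated cases will be estimated with weighted linear regression models in the case of continuous outcomes". The section adds: "Robust standard errors will be calculated". It names no covariates for the outcome model.

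**The concern.** Matching with replacement lets one untreated person serve as control for several rehabilitants. That person supplies one outcome value, which enters the weighted regression with a larger weight. The 828 in the power calculation is then the number of slots filled, not the number of persons, and the control mean is less precise than the mean of 828 independent people.

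The design has little margin: 0.82 is just above the customary 0.80. If the calculation ignores reuse, the article claims a power that the unadjusted analysis does not have. A null result would then be read against a stated power that is somewhat too high. This matters because the Background describes the existing German evidence as contradictory and includes a randomised trial without group differences.

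**Working it through.** **Inputs from the article.** 45,000 persons mailed (Abstract). Baseline response 40%, linkage consent 80%, back pain 40%, rehabilitation 8%, follow-up response 60%; SMD 0.2; two-sided alpha 0.05; 276 and 828 (Sample size estimation). Three controls per case, with replacement (Propensity score matching).

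**Step 1: participant flow.**
- Back pain cohort: 45,000 x 0.40 x 0.80 x 0.40 = 5,760, as stated in the Abstract.
- Rehabilitants at follow-up: 5,760 x 0.08 x 0.60 = 276.5, i.e. the stated 276.
- Untreated pool at follow-up: 5,760 x 0.92 x 0.60 = 3,179.5, about 3,180.
- Slots: 3 x 276 = 828.

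**Step 2: reproduce the stated power.** With the outcome SD set to 1 and n_c controls, power is about Φ(0.2 / √(1/276 + 1/n_c) − 1.96).
- n_c = 828: √(0.003623 + 0.001208) = 0.06950; 0.2 / 0.06950 = 2.878; Φ(0.918) = 0.821.
- The noncentral t version gives 0.820.

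So 0.82 is the two-sample power for 828 independent, equally weighted controls.

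**Step 3: effective number of controls.** If control i is used w_i times, the weighted control mean has the precision of n_eff = (Σw_i)² / Σw_i² independent persons. This equals 828 only if nobody is reused.

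The n_eff values come from simulating selection of the three nearest neighbours with replacement, for 276 treated persons and a pool of 3,180. The logit of the propensity score was taken as normal with equal variance in both groups. The nearest-neighbour rule, the normal shape and the c-statistic are assumptions; the article gives none of them.

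| c-statistic (assumed) | Different controls | n_eff | √(1/276 + 1/n_eff) | Power, SMD 0.2 |
|---|---|---|---|---|
| 0.50 (identical distributions) | 716 | 637 | 0.07206 | 0.793 |
| 0.70 | 664 | 546 | 0.07386 | 0.773 |
| 0.76 | 618 | 460 | 0.07614 | 0.747 |
| 0.80 | 576 | 382 | 0.07900 | 0.716 |

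**Step 4: checks.**
- Simulating the weighted mean difference directly, with a robust standard error, gave power 0.79, 0.77, 0.76 and 0.73 for the four rows.
- Matching before loss to follow-up gave practically the same effective numbers.
- A hand check needs no simulation. If the 828 slots fell purely at random over the pool, which is more favourable than selection by score, the mean use per control would be 828 / 3,180 = 0.26. Then n_eff is about 828 / 1.26 = 657 and power is 0.796.
- For power 0.80: 1/n_eff = (0.2 / 2.8016)² − 1/276 = 0.005096 − 0.003623 = 0.001473, so n_eff must be about 679. None of the cases above reaches this.

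**Step 5: what covariate adjustment would have to recover.** Power returns to 0.82 if covariates explain a share R² = 1 − (1/276 + 1/828) / (1/276 + 1/n_eff) of the outcome variance.

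| n_eff | R² | Correlation √R² |
|---|---|---|
| 637 | 0.07 | 0.26 |
| 546 | 0.11 | 0.34 |
| 460 | 0.17 | 0.41 |
| 382 | 0.23 | 0.48 |

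**The case against.** The other side has several good arguments.

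- **No sum is wrong.** 5,760, 276 and 0.82 all reproduce. This stands: the fault is a mismatch between the calculation's inputs and the matching rule. A reader who inferred a miscalculation would be mistaken.
- **The loss is small.** The 276 rehabilitants dominate the variance. The SMD detectable with 80% power is 2.8016 x √(1/276 + 1/n_eff): 0.195 for 828 controls, 0.202 for 637, 0.207 for 546 and 0.221 for 382. This stands, and it limits the weight of the point. Calling the study inadequately powered would go too far.
- **The size depends on overlap, which the article does not give.** This stands for everything below about 0.79. It does not touch the direction, because any reuse lowers the effective number.
- **Baseline pain disability is measured, and the planned regression could carry it.** Step 5 shows that a modest correlation would restore 0.82. But the article neither states such adjustment nor uses it in the calculation, so this is a remedy rather than an answer.
- **The pool could supply 828 different controls.** It could without replacement, but the article chooses replacement.
- **Robust standard errors already deal with unequal weights.** This stands for the analysis: with each control entered once with its match weight, they reflect reuse. They do not change the power stated at the planning stage.

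A reader might also infer that the caliper will cost treated cases. The article uses it only if balance requires it, and gives no basis for quantifying a loss.

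**Conclusion.** The point holds, with moderate weight. The stated 0.82 belongs to a design with 828 different, equally weighted controls, and the matching rule does not deliver that design. Unadjusted power for SMD 0.2 is about 0.79 at best, roughly 3 percentage points below the stated figure. It is about 0.77 to 0.72 if the c-statistic is 0.70 to 0.80.

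The direction follows from the article alone. The best-case figure rests on the article's expected pool and on nearest-neighbour selection. The lower figures rest also on the assumed separation of the groups. The article's Background reports that users and non-users of rehabilitation differ in health, work ability and sickness absence, so some separation is plausible, but its extent is not known.

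Two stronger readings are not supported. One is that a specific lower power is the protocol's own expectation: without an overlap figure, no such value can be attributed to it. The other is that the planned standard errors are wrong: weighted regression with robust standard errors can reflect the reuse of controls.

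**What to change.** Change the section Sample size estimation in one of two ways.

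1. Restate the power using the expected effective number of controls under 1:3 matching with replacement, and name the overlap assumption behind it. Unadjusted, the figure would be at most about 0.79. Any value for poorer overlap should be labelled as an assumption.
2. State in Estimating the treatment effect that the weighted regression adjusts for baseline pain disability, and recompute the power for that model from the effective number of controls and an assumed baseline-to-follow-up correlation. For orientation, 0.82 would be recovered with a correlation of about 0.26 at an effective 637 controls and about 0.48 at 382.

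Either way the cost is a short recalculation and a few sentences. No extra participants are needed, and neither the matching rule nor the robust standard errors have to change on this ground.

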**Fig. 1 Fig1:**
[figure not shown]
Flow of participants

### Recruitment

After the sample has been drawn potential study participants will be contacted by post by the GPI. The first mailing of the baseline survey will include a personalised cover letter, information about the study, a consent form, and two envelopes (a prepaid envelope and a small envelope for the consent form). The prepaid envelope is to be used to send the completed questionnaire and the envelope containing the consent form to the university. The project staff at the university will collect the consent form envelopes and pass them on to the relevant GPI employees without opening them, as they contain personal data. The GPI employees will check off those who have provided informed consent against a study list and inform the scientists at the university by transferring the identification numbers for consenting participants. Participation is voluntary and participants are free to withdraw their consent at any time without any consequences.

One, four and five weeks after the initial mailing of the questionnaire reminders will be sent to potential study participants. The first reminder takes the form of a short thank-you letter to remind the recipient about the study and the questionnaire they received recently. The second reminder is sent 3 weeks after the first reminder and contains all of the above-mentioned study material. This reminder is only sent to persons who have not yet returned their questionnaire. The third and final reminder is sent 1 week after the second reminder, once again it highlights the importance of the recipient’s participation in the study and thanks them in advance for their support. The final reminder also contains a link to the study website (www.rehab-bp.de) which will inform about the study and its findings.

During the third study year, a second survey will be conducted. The format is the same as for the first survey: a first mailing comprising a cover letter, questionnaire and prepaid envelope, a second mailing consisting of a short reminder, a third mailing containing the same material as the first, sent only to those who have not yet returned their questionnaires, and a fourth mailing consisting of a final short reminder. The schedule for enrolment, interventions and assessments is displayed in Table 1.

**Table 1 Tab1:**
[figure not shown]
Time schedule of enrolment, interventions and assessments

### Data management

Questionnaires will be scanned and verified by an electronic data capture system and exported to statistical software packages for further analysis. Scanning and verifying will be done by trained research assistants who will compare the imported data with the original questionnaire data. Administrative data will be extracted by the GPI North and GPI Central Germany and personal data will be removed and replaced by the unique study identifier. These administrative data will be transferred to the principal investigators (MB, WM). Questionnaire and administrative data can be linked via the unique study identifier.

The authors of the protocol will be responsible for data management in the study. Data access will be limited to the authors and the team of research assistants.

### Outcomes and other measures

The questionnaire used in this study will include items on various barriers to rehabilitation utilisation, primary and secondary outcomes and some additional variables. Data on additional outcomes will be extracted from administrative records (i.e. individual pension insurance accounts). These administrative data will be provided by the GPI North and GPI Central Germany. A complete list of all measured constructs, measurement points and expected scaling is shown in Table 2.

**Table 2 Tab2:** Measures, assessment, expected scaling and measurement points

Outcome	Source and reference	Total score	Scaling	Baseline	Follow-up
Primary Outcome					
Pain disability	CPQ [48, 49]	0 to 100	metric	X	X
Secondary Outcomes					
Pain intensity	CPQ [48, 49]	0 to 100	metric	X	X
Days of disability	CPQ [48, 49]	0 to 90	metric	X	X
Pain self-efficacy	PSEQ [50, 51]	10 to 60	metric	X	X
Fear avoidance beliefs	Modified FABQ subscales [52, 53]	0 to 18	metric	X	X
General health	COPSOQ [54, 55]	0 to 10	metric	X	X
Depressive symptoms	PHQ-8 [56, 57]	0 to 24	metric	X	X
Work ability	WAS [58]	0 to 100	metric	X	X
Subjective prognosis of employability	SPE [59]	0 to 3	ordinal	X	X
Healthcare utilisation:	Own development				
Use of pharmaceuticals			binary	X	X
Outpatient visits to physicians			metric	X	X
Utilisation of therapy			metric	X	X
Hospital stay			binary	X	X
Days of sick leave		0 to 365	metric	X	X
Days in receipt of sickness absence benefits	GPI registers		metric	X	X
Days in regular employment	GPI registers		metric	X	X
Application for disability pension	GPI registers		binary		X
Grant of a disability pension	GPI registers		binary		X
Other measures					
Comorbidity	Modified subscale of the SCQ [60, 61]	0 to 15	metric	X	
Health behaviour	Own development				
Physical exercise			binary	X	
Cigarette smoking			binary	X	
Body Mass Index			metric	X	
Self-help group or organisation			binary	X	
Employment status	Own development		nominal	X	
Job profession	Own development		nominal	X	
Working hours	Own development		ordinal	X	
Fixed-term job contracts	Own development		nominal	X	
Shift work	COPSOQ [54, 55]		nominal	X	
Size of enterprise	COPSOQ [54, 55]		ordinal	X	
Physical demands	FEBA [62]	0 to 15	metric	X	
Psychological demands	COPSOQ [54, 55]	0 to 100	metric	X	
Support by supervisor and colleagues	COPSOQ [54, 55]	0 to 100	metric	X	
Atmosphere at work	COPSOQ [54, 55]	0 to 100	metric	X	
Job insecurity	COPSOQ [54, 55]	0 to 100	metric	X	
Overall job satisfaction	COPSOQ [54, 55]	0 to 100	metric	X	
Workplace bullying	[63]	0 to 100	metric	X	
Cognitions about experiences with rehabilitation services	[64]				
Former medical rehabilitation services			binary	X	
Subjective need for rehabilitation			binary	X	
Intention to apply for medical rehabilitation			binary	X	
Knowledge of rehabilitation application procedures			metric	X	
Negative outcome expectations			metric	X	
Social support from family and friends			metric	X	
Social support from physicians and therapists			metric	X	
Socio-demographic data	Own development		metric/nominal	X	

*COPSOQ* Copenhagen Psychosocial Questionnaire, *CPQ* Chronic Pain Grade Questionnaire, *FABQ* Fear-Avoidance Beliefs Questionnaire, *GPI* German Pension Insurance, *FEBA* Fragebogen zur subjektiven Einschätzung der Belastungen am Arbeitsplatz (questionnaire on job demands), *PSEQ* Pain Self-Efficacy Questionnaire, *PHQ-8* Patient Health Questionnaire (8-item version), *SCQ* Self-Administered Comorbidity Questionnaire, *SPE* subjective prognosis of employment status, *WAS* work ability score

#### Primary outcome

Pain disability will be the primary outcome in our analyses of the effectiveness of medical rehabilitation and will be assessed at baseline and follow-up. Three items from the German version of the Chronic Pain Grade Questionnaire will be used to assess pain disability [48, 49]. These items deal with the extent to which pain interferes with important life domains, including daily living, leisure time and work. Because it includes the work domain this measure also covers work ability, which is the primary focus of GPI-approved rehabilitation services. The German version of the Chronic Pain Grade Questionnaire has been shown to be a reliable, valid and useful instrument [49]. Items are scored from zero to ten points, with higher scores indicating greater disability. Item scores are averaged and multiplied by ten to give a total pain disability score ranging from 0 to 100 points.

#### Secondary outcomes

The secondary outcomes of our analyses of the effectiveness of rehabilitation will be assessed at baseline and follow-up.

##### Pain intensity and disability days

Four items from the Chronic Pain Grade Scale will be used to assess pain intensity (three items) and days of disability (one item) [48, 49]. The pain intensity items cover current, worst and average pain in the last 3 months. The items are scored from zero to ten points, with higher values indicating stronger pain. Items are averaged and multiplied by ten to give a total pain intensity score of between 0 and 100 points. Days of disability are the number of days in the previous 3 months when the respondent could not carry out his or her usual activities due to pain. The variables pain disability, pain intensity and days of disability are used to derive a pain grade. Pain grades range from no pain to severely limiting pain [2, 48, 49]. Pain grade I represents low intensity pain associated with limited disability, grade II represents high intensity pain and limited disability, grade III represents moderate disabling pain regardless of pain intensity, and grade IV represents severely disabling pain regardless of pain intensity [48].

##### Pain self-efficacy

Self-efficacy with respect to coping with back pain will be assessed with the German adaptation of the Pain Self-efficacy Questionnaire (PSEQ; German: Fragebogen zur Erfassung der schmerzspezifischen Selbstwirksamkeit, FESS) [50, 51]. The FESS measures belief that one will be able to perform various activities despite one’s pain. The ten items are rated on a 6-point scale from 1 (‘not at all confident’) to 6 (‘completely confident’). Total scores range from 10 to 60, with higher scores indicating greater pain self-efficacy. The FESS has been shown to be a valid instrument for the evaluation of therapeutic success in the context of pain research [51].

##### Fear avoidance beliefs

The German version of the Fear Avoidance Belief Questionnaire (FABQ) [52, 53] comprises two subscales. In this study three items of the physical activity scale will be used to assess belief that physical activity causes or compounds back pain. Additionally, three items of the work subscale will be used to assess beliefs about how work might affect one’s back pain. The 7-point scale ranges from 0 (‘completely disagree’) to 6 (‘completely agree’). Score for items from both scales will be added to yield a sum score ranging from 0 to 18 points, with higher values indicating stronger fear avoidance beliefs.

##### General health

General health will be assessed with one item from the Copenhagen Psychosocial Questionnaire with an 11-point scale (0 ‘worst imaginable health state’ to 10 ‘best imaginable health state’) [54, 55].

##### Depressive symptoms

Depressive symptoms will be measured using the 8-item depression module of the Patient Health Questionnaire (PHQ-8), which is recommended for research purposes [56, 57]. Items assess the frequency of depressive symptoms during the last 2 weeks and responses are given on a 4-point scale (0: ‘not at all’ to 3: ‘nearly every day’). Total scores range from 0 to 24 points.

##### Work ability

Self-rated work ability is assessed using the Work Ability Score (WAS) [58]. This 11-point scale ranges from 0 (‘completely unable to work’) to 10 (‘maximal work ability’).

##### Subjective prognosis of employability

Three items will be used to assess whether participants believe they will remain at work until retirement, whether they assume that their health is permanently jeopardised and whether they intend to request a disability pension [59]. Dichotomous item scores are summed to give a total score ranging from 0 to 3 points, with higher values indicating a less favourable prognosis.

